| Pneumococcal vaccination up to date                                                                                                                                                                                                                                                                                                                                                                                                                                                                   | Vaccination status                                                                                                                    |
| Covid-19 vaccination                                                                                                                                                                                                                                                                                                                                                                                                                                                                                  | Vaccination status                                                                                                                    |
| Clinical measurements: 
 
– Cholesterol (mmol/L)
 
– LDL (mmol/L)
 
– HDL (mmol/L)
 
– Triglycerides (mmol/L)
 
– Creatinine (µmol/L)
 
– eGFR (ml/min/1.73m^2)
 
– uACR (mg/mmol)
 
– Random BGL (mmol/L)
- non-fasting, blood glucose test performed at the health service
 
– HbA1c (mmol/mol)
HbA1c (%)
 
– Systolic BPM (mm/Hg)
 
– Diastolic BPM (mm/Hg)
 
 | Identify proportion within recommended range                                                                                          |
| Number of failed follow up attempts in past 12 months                                                                                                                                                                                                                                                                                                                                                                                                                                                 | Service utilisation                                                                                                                   |

|                                                                                                                                                                                                                                                                                                                                                                                                                                         |                                                     |
|-----------------------------------------------------------------------------------------------------------------------------------------------------------------------------------------------------------------------------------------------------------------------------------------------------------------------------------------------------------------------------------------------------------------------------------------|-----------------------------------------------------|
| Related conditions of clients with diabetes: 
 
– Coronary heart disease
 
– Stroke or TIA
 
– Peripheral artery disease
 
– Congestive heart failure
 
– Chronic kidney disease
 
– Depression
 
– Hypertension
 
– Dyslipidaemia
 
– Cardiac dysrhythmia
 
 | Understand burden of chronic disease among clients. |
| Referrals to diabetes educator, diabetes specialist, optometrist, podiatrist, dietician, dentist, psychologist, social worker, exercise physiologist, mental health screening                                                                                                                                                                                                                                                    | Understand quality of care referral                 |

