#### **4. HYPOTHESIS**

It is hypothesized that the primary health care services whose workforce participate in the training program will have:

- a workforce with increased knowledge, confidence, and skills to manage diabetes within the local primary health care setting,
- in the longer-term, improvements in the quality of diabetes care provided and patient biomedical outcomes.

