| Client level                                           | 
Eligibility criteria: People with diabetes who have attended the participating health service and who fulfil the following criteria at the time of record review meet the following criteria:
 
 
• Both males and females who aged 18 years and over;
 
• identify as Aboriginal or Torres and Strait Islander people;
 
• have a confirmed diagnosis of T2DM and/or a HbA1c <math>\geq 6.5</math> mmol/L;
 
• have attended the health service at least twice in the preceding 12-month period;
 
 
Those who meet the eligibility criteria become the study population in which the below variables are extracted.
 |
| Client ID                                              | Service unique record ID created and provided by the health service so that no identifying data is provided to the study team                                                                                                                                                                                                                                                                                                                                                                                                                                                                                                                                                                      |
| Month & Year of Birth                                  | To estimate age                                                                                                                                                                                                                                                                                                                                                                                                                                                                                                                                                                                                                                                                                    |

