## **Secondary Outcomes**

Provision of evidence-based care and patient biomedical outcomes will be summarised using counts, means and percentages and differences between time collection points reported. Patients will be stratified by for example, age, gender, diabetes type and existing comorbidities.

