### **c. Waiver of consent**

A waiver of consent is being requested to access pre-existing, de-identified patient information to perform the medical record review. The data requested is collected as part of routine client care. Data will only be re-identifiable by the health service that provided the de-

identified data. Justification for a waiver of consent under section 2.3.10 (a-i) of the National Statement on Ethical Conduct in Human Research is provided as follows:

**a) involvement in the research carries no more than low risk (see paragraphs 2.1.6 and 2.1.7, page 18 of the National Statement) to participants**

The use of patient data in the context of this study carries low risk. Risk is associated with maintaining data security and anonymity, for which the project has strict control measures and monitoring in place. The use of patient data in the context of this study is to determine the effectiveness of the training program on quality of care and patient outcomes. To further protect the identity of individual clients, the data of all clients will be collected and analysed in aggregate at the service level as opposed to individual outcomes.

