**b) the benefits from the research justify any risks of harm associated with not seeking consent**

Aboriginal Health Workers and Practitioners have typically participated in countless hours of training across a wide range of areas. Most training is not evaluated for effectiveness. The program logic of this study is that effective training in diabetes management leads to improvements in evidence-based knowledge, skills and practice and positive attitudes of diabetes which in turn leads to improved quality of care and patient outcomes. It is important that where possible such end points are evaluated to understand future investment of health workers and training providers in time and resources and critically the benefit to clients.

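### In-range proportions and means from routine records, compared between audits, can show a change in testing as a change in patients' control

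*Protocol*

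**What the plan says.** Protocol section 10.d lists the variables to be taken from electronic medical records. For BMI, waist circumference and the block of clinical measurements (lipids, creatinine, eGFR, uACR, random glucose, HbA1c, blood pressure), the justification column reads "Identify proportion within recommended range". No denominator is given, and nothing is said about clients with no result.

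The source population is every eligible client: "Those who meet the eligibility criteria become the study population in which the below variables are extracted". Eligibility applies to people "who fulfil the following criteria at the time of record review", so the population is formed afresh at each audit.

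Section 11.a (Secondary Outcomes) says that evidence-based care and "patient biomedical outcomes will be summarised using counts, means and percentages and differences between time collection points reported". Section 14.c, item (a), adds that "the data of all clients will be collected and analysed in aggregate at the service level as opposed to individual outcomes".

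The purpose goes beyond description. Section 4 hypothesises, in the longer term, "improvements in the quality of diabetes care provided and patient biomedical outcomes". Section 14.c, item (b), sets out a chain from training to knowledge, skills and practice, "which in turn leads to improved quality of care and patient outcomes".

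For GP management plan reviews, foot checks and cardiovascular risk assessments, section 10.d gives a measure of whether the task was done on time. It gives none for laboratory tests, blood pressure, BMI or waist.

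**The concern.** Routine records hold a value only when someone took a measurement. If staff become better at guideline care, one likely result is that more clients are measured. The in-range proportion and the mean among tested clients both depend on who was measured as well as on how well they are controlled. A difference between two audits can therefore mix the two effects.

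Choosing a denominator does not by itself separate them. If all eligible clients form the denominator, an untested client counts as not in range, so more testing raises the figure. If only tested clients form it, the newly tested change the mix.

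The audits are placed ideally at T1, T4 and T6 (section 10.c). By T4 both groups have had the modules and onsite support, so a difference between these audits is a before-after contrast. At stake is the longer-term hypothesis: the trial could report better or worse control when mainly the testing rate had moved.

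**Working it through.** The Protocol states no figure for these outcomes, so there is none to reproduce. The check holds every patient's true control and the eligible population fixed, and lets only testing change.

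**Inputs.** None is in the documents; all are assumptions.
- t0, t1: share of eligible clients tested at the earlier and later audit
- pA: share in range among those already tested
- pB: share in range among the newly tested

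**Formulas**
- All eligible clients: before = t0·pA; after = t0·pA + (t1 − t0)·pB; difference = (t1 − t0)·pB.
- Tested clients only: before = pA; after = [t0·pA + (t1 − t0)·pB] / t1; difference = (t1 − t0)·(pB − pA) / t1.

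When testing rises, the first difference is positive whenever pB is above zero. The second is zero if pB = pA, negative if pB < pA and positive if pB > pA. The signs are opposite only when pB is above zero and below pA.

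**Numbers, with t0 = 0.60, t1 = 0.80, pA = 0.40**

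| pB | All eligible | Difference (points) | Tested only | Difference (points) |
|---|---|---|---|---|
| 20% | 24% to 28% | +4.0 | 40% to 35% | −5.0 |
| 30% | 24% to 30% | +6.0 | 40% to 37.5% | −2.5 |
| 40% | 24% to 32% | +8.0 | 40% to 40% | 0.0 |
| 50% | 24% to 34% | +10.0 | 40% to 42.5% | +2.5 |

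For the 30% row: 0.60 × 0.40 = 0.24; 0.24 + 0.20 × 0.30 = 0.30; 0.30 / 0.80 = 0.375.

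**Range.** The grid took testing from 50% to 60%, 60% to 80%, 70% to 90% and 80% to 90%. Each was combined with pA = 40% and pB from 20% to 50%, and with pA = 50% and pB = 25%. The all-eligible figure moved by +2.0 to +10.0 points and the tested-only figure by −6.3 to +2.5 points, with no true change.

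**Means.** With testing from 60% to 80% and assumed mean HbA1c of 8.0% in the already tested and 9.0% in the newly tested, the mean among tested clients becomes (0.60 × 8.0 + 0.20 × 9.0) / 0.80 = 8.25, a shift of +0.25. With 7.5% in the newly tested it becomes 7.875, a shift of −0.125. If the two groups are equal there is no shift.

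**What three categories would show (30% row).** Before: 40% not measured, 24% in range, 36% out of range. After: 20% not measured, 30% in range, 50% out of range (36 + 20 × 0.70). Both measured categories rise because the unmeasured one falls by 20 points. The reader can see that the 6-point gain came with a large change in testing.

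**The case against.** Denominators and missing values for a descriptive secondary outcome are ordinary SAP content, and Attachment 14, which holds the variable details, is not shown. The text quoted for the measurements is a justification for requesting data rather than an analysis rule. Section 11.a also lists counts and means, and nothing there forbids showing numbers measured. Table 3 already keeps quality of care (up to 35 variables) apart from patient behaviour and clinical outcomes (up to 8), and testing rates may be among the 35.

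Much of this is fair, and it limits the point. The absence of a denominator is not itself the finding. What remains is that the summaries the Protocol does name, in-range proportions and means compared between audits in aggregate, cannot separate testing from control under either denominator, and stating one later would not change that.

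A reader might infer more than the documents support:
- *That the training is designed to raise testing.* No section says so for laboratory tests or blood pressure. It is an inference from the quality-of-care hypothesis.
- *That a testing change must appear as a change in control.* Over all eligible clients it does so, provided untested clients count as not in range and some newly tested client is in range. Over tested clients nothing moves if the newly tested resemble the rest.
- *That the denominator decides the sign.* This needs worse control among the newly tested. At 50% in range both differences are positive.
- *That within-client change should be the main analysis.* Section 14.c, item (a), commits to aggregate analysis. No section says that client IDs stay the same across extractions. Clients measured twice are also a selected group.

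**Conclusion.** The point holds in a conditional form. As summarised, a change in testing between audits can read as a change in biomedical control. On the assumed grid, with no patient changing, the artefact is +2.0 to +10.0 points over all eligible clients and −6.3 to +2.5 points over tested clients. These are illustrations: the documents give no testing rate and no level of control. The argument rests on two assumptions, that testing changes between audits and, for the tested-only denominator and for means, that the newly tested differ from those already tested. Both are plausible, and neither is stated.

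The outcome is secondary and descriptive, and the primary outcomes are not affected. The change is still worth making, because a stated hypothesis depends on these summaries and the remedy is cheap.

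**What to change.** For each clinical measurement, and for BMI and waist circumference, report at each audit three proportions over all eligible clients: not measured, measured in range, measured out of range. Treat the proportion measured as a quality-of-care result. State that no conclusion about biomedical change will be drawn from the in-range proportion or the mean without the change in the proportion measured beside it.

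The table makes a testing change visible. It does not prove how much of a difference is due to testing, and it does not hold the client population fixed between audits.

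A comparison limited to clients measured at both audits can be at most an optional sensitivity analysis. It needs IDs that are stable across extractions, must be reconciled with the commitment to aggregate analysis in section 14.c, item (a), and should be labelled as a selected subset.

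The main change costs a few lines in section 11.a or the SAP and some extra tabulation. It needs no new variables, because the extraction already covers all eligible clients.

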#### **e. Data linkage**

Not applicable.

#### **f. Safety considerations**

Potential risks of participating in the research and strategies to mitigate and manage them are outlined below. It is anticipated that any risks to participants will be minimal and limited to discomfort or inconvenience, as defined by the *National Statement section 2.1*. The benefits to participating in the research are believed to justify any potential risks. All risks will be brought to the attention of the Principal Investigator by the research team member/s and/or a participant/s and/or steering committee member. The Principal Investigator will assess if the risk needs to be elevated to the research investigators based on its severity. A risk register will be kept that identifies the risk and severity of the risk, who was affected (not name but if they were a participant, service manager, etc.), who the risk was reported to, the immediate action and how the same risk in the future will be minimized or mitigated. It is the responsibility of the individual who raises the risk with the Principal Investigator to complete the risk register or the Principal Investigator if a participant or someone other than a study team member. The risk register will be included in the papers of each Investigator meeting.

It is possible that participants may be inconvenienced by the work and/or personal time required to participate in the research. This potential burden has been considered in the design of the training program, by ensuring that the program is flexible and obtaining support from service management as an eligibility to be in the study.

Obtaining consent from participants to check on their wellbeing will be discussed in the consent process and is included in consent forms and the distress protocols.

**Peer Support Network sessions:** Differences in opinions/ideas may cause conflict between participants, which could lead to participants feeling upset or uncomfortable in contributing to discussion. In the event this occurs, the PSN Facilitator will follow the PSN Distress Protocol (Attachment 15), which may include pausing or terminating the session. The PSN Facilitator will notify the Principal Investigator of the incident and document the incident. A follow up wellness check will be conducted with the affected participant(s). If conflict arises between the PSN Facilitator and participating AHW/Ps during the online PSN sessions, the PSN Facilitator will terminate the session and contact the Principal Investigator for support.

**Onsite Support:** Professional/personal differences may arise between the participants and the OS Facilitator. If this occurs, participants can contact a member of the research team as indicated in the Participant Information Sheet. Any risks that arise in the provision of routine client care should be dealt with according to the policies in place at the participant's health service. A distress protocol will be followed if distress should arise (Attachment 16).

**Interviews enablers and barriers:** In the unlikely event that participants become upset while reflecting on their experience of the education program, the interviewer will follow the Individual Interview Distress Protocol (Attachment 17).

**Systems assessment:** Differences in opinions/ideas may cause conflict between participants, which could lead to participants feeling upset or uncomfortable in contributing to discussion. In the event this occurs, the Facilitator will follow a distress protocol (Attachment 18), which may include pausing or terminating the session. The Facilitator will notify the Principal Investigator of the incident and document the incident. A follow up wellness check will be conducted with the affected participant(s). If conflict arises between the Facilitator and participating staff during the focus group, the Facilitator will terminate the session and contact the Principal Investigator and Service Manager for support.

## **g. Data monitoring**

The Study Manager, with guidance and support of the Principal Investigator, [name] will manage the data. All data will be entered into a computerised database with regular automated backups. Checks for accuracy and completeness will be done shortly after data collection. Computer codes and site randomisation schedule will be restricted to the Study Manager and Principal Investigator and maintained in a secure server unavailable to the data analyst.

Status of survey completion for each participant can be seen in a separate part of the RedCap survey that is not connected to individual survey responses. This shows whether the survey has been completed, started but not completed and not yet started. RedCap capability allows for reminders with survey links to be sent to individual participants yet to complete the survey.

For the research documentation, the PSN and OS Facilitators will keep a reflective journal that will describe the session from their perspective, barriers and enablers to successful

uptake and impact and what could be improved. As the Facilitators are research team members, on advice from the HREC sub-committee, they are not considered research participants and their documentation can be used to inform improvements of the study and be used to describe and evaluate the study. They will record the date of the session and document:

- Detailed description of what was done during each session
- From the Facilitators' perspective, what went well in the session and what could have been done better and potential mitigation or strategies for improvement.
- They will be asked not to record individual or identifying information of individual participants.

These will be collected within 5 days of each session by the Study Manager.

#### **h. Protocol deviations**

The Principal Investigator with all Investigators will monitor protocol deviations and/or adverse events. These will be reported to the SA Department for Health and Wellbeing HREC and site-specific research governance officers within 72 hours of identification of the event. Corrective actions will be implemented promptly.

